### Interviews following ROR

2.3

After every successful ROR, participants will be subjected to the following 6-question interview (and provided with the following possible answers):

Did you have any sensations or thoughts before you were awakened? Yes/No/Not sure/NothingDid you hear the tones? Yes/No/Not sureDo you think you were awake, having a dream or unconscious? Awake/Dream/Unconscious/Not sureDid you hear one or two different tones? One/Two/Not sure/NothingWas this experience more centered on yourself or on the environment? Myself/Environment/NothingDid you rather think, or did you see many things? Think/See/Not sure/Nothing

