The first and third questions will verify that participants were (un)conscious during the period of unresponsiveness and the second question will verify the (dis)connectedness of participants during the period of unresponsiveness. The last three questions will serve two purposes: to gather more detailed information on the experience during the period of unresponsiveness and to check the consistency of the reports. Probing the presence of the experience/perception of sounds will strengthen the reliability of the answers to the first two questions (e.g., the participant might answer that he/she did not hear any sounds, but then answer the question “did you hear one or two tones?” with “two”). This interview will identify four different states: (1) awakening without any recall of experiences; (2) connected dreaming; (3) disconnected dreaming and (4) wakefulness. State 1 will be discarded as it cannot be classified in either of the two categories of interest in this study. Connected consciousness (i.e., connected dreaming) will be considered to have occurred during the unresponsive period if participants answered “Yes” to questions number 1–2 and disconnected consciousness if participants replied “Yes” to question 1 and “No” to question 2. In the case of conflicting answers, we will consider participants to have been connected conscious if they provide a positive response to at least one question amongst numbers 1,5,6 or if they respond with “having a dream” to question number 3, in addition to a positive response to at least one question amongst numbers 2 and 4. Participants responding with “awake” to question number 3 will be excluded, as they will be considered not to be in a state of connected consciousness during a dream-like state but rather awake. If participants replied with “No/Nothing” to question number 2–4 and positively to at least one of the questions investigating their experience (i.e., question number 1,3,5,6) they will be considered having been disconnected conscious during the unresponsive period. Participants will be acquainted in advance with the different questions and possible answers to ensure full understanding of each question. To rule out potential arousals during fMRI acquisitions, subjects will be monitored continuously throughout the acquisition via an eye-tracking camera (EyeLink 1000plus system from SR Research, Ltd) – the eye-tracker will be used for online monitoring but not for offline analysis. In case of eye opening, MRI acquisition will be interrupted, and we will wait for participants to spontaneously fall unresponsive again. If, after 15 min, LOR does not occur, we will increase the propofol concentration up to three times in 0.1 μg.ml^−1^ increments.

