## Discussion

5

Identifying the neuroimaging signatures of disconnected consciousness during sleep or anesthesia is a particularly difficult undertaking, owing to the inherent challenges in ascertaining the kind of experience (or lack thereof) a sleeping or sedated subject is having. This work aims to advance the investigation of the neural basis of sensory disconnection by achieving a more precise identification of this state, distinguishing it from states of unconsciousness and connected consciousness. In classical anesthesia studies, differentiation between these states was typically overlooked, with anesthetized subjects categorized as either conscious or unconscious based on behavioral responsiveness or explicit recall after anesthesia. In this study, we will overcome previous limitations by awakening participants immediately after auditory stimulation and asking them whether they were connected or disconnected before being awakened. This procedure, by minimizing amnesic effects of anesthesia and relying on subjective reports rather than (un)responsiveness to ascertain the subject’s state, enables a more accurate account of the subject’s experience.

This work represents also a notable progression in mitigating biases linked to contrastive, between-state paradigms, wherein two physiologically distinct states are compared (Koch et al., 2016; Boly et al., 2017). In this study, we ensure that participants are unresponsive and are in a dream-like state before awakening, in both connected and disconnected consciousness conditions. As a result, the conditions of connected and disconnected consciousness are contrasted within the same physiological state, i.e., both connected and disconnected participants are unresponsive and in a dream-like state.

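### A tone heard can by itself meet the connected-consciousness rule, and neither group must report a dream, so the claim that both states are dream-like is not secured

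*Protocol article*

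**What the plan says.** The protocol article, section 2.3 (Interviews following ROR), lists six questions asked after each successful awakening. Question 1 is "Did you have any sensations or thoughts before you were awakened". Question 2 asks whether the tones were heard. Question 3 offers awake, dream, unconscious or not sure. Question 4 asks how many different tones were heard, question 5 whether the experience centred on the self or the environment, and question 6 whether it was thinking or seeing. On the roles of these questions the section states: "The first and third questions will verify that participants were (un)conscious during the period of unresponsiveness".

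The classification rules are:

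- CC, main rule: "Connected consciousness (i.e., connected dreaming) will be considered to have occurred during the unresponsive period if participants answered “Yes” to questions number 1–2".
- DC, main rule: "disconnected consciousness if participants replied “Yes” to question 1 and “No” to question 2".
- CC when answers conflict: "they provide a positive response to at least one question amongst numbers 1,5,6", or a dream answer to question 3, together with a positive answer to question 2 or 4.
- DC, fallback: the tones denied, and participants answering "positively to at least one of the questions investigating their experience (i.e., question number 1,3,5,6").
- Exclusion: "Participants responding with “awake” to question number 3 will be excluded".

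The Discussion (section 5) says the study ensures a matched state before awakening, so that "both connected and disconnected participants are unresponsive and in a dream-like state".

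**The concern.** The study presents itself as varying connection to the environment while holding the unresponsive, dream-like state constant. The Introduction faults earlier work because its contrasts could reflect responsiveness or arousal instead. The label 'connected dreaming' is given without any answer that establishes dreaming, and the same question 1 does different work in the two groups. In CC the tones can be the whole of the reported experience. In DC the tones are denied, so something else must have been experienced.

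If a material share of CC sessions are tone-only, a CC–DC difference in cortical response, connectivity or BOLD oscillations could partly reflect the presence or absence of other experience rather than sensory gating. The group-level model in section 2.9.5 adjusts for propofol concentration and time to ROR. As described, it has no term for the question 3 answer or for dream content.

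**Working it through.** The plan gives no figure to reproduce here. The check applies the printed rules to answer patterns.

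**Step 1: can a tones-only report become CC?** Take question 1 'Yes' (a tone is a sensation, and the printed wording does not set the tones aside), question 2 'Yes', question 3 'Unconscious' or 'Not sure', question 4 'Two', question 5 'Environment' or 'Nothing', question 6 'Nothing'. The main CC rule is met and the 'Awake' exclusion does not apply, so the session is CC. If 'Unconscious' were treated as a conflict, the conflict rule would still return CC, because questions 1 and 2 are both positive. Even with question 1 'No', the version with 'Environment' at question 5 is CC under the conflict rule.

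**Step 2: the mirror case.** Remove the tones and leave no other content: questions 1 and 2 'No', question 3 'Not sure', questions 4 to 6 'Nothing'. This cannot be DC; it is discarded or unclassified. DC therefore always needs a reported experience other than the tones, and CC does not.

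**Step 3: is a dream required in either group?** The six questions have 4 × 3 × 4 × 4 × 3 × 4 = 2,304 possible answer patterns. Conventions used:

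- Positive means 'One' or 'Two' at question 4, 'Myself' or 'Environment' at question 5, and 'Think' or 'See' at question 6.
- The DC fallback's reference to questions 2–4 is read as questions 2 and 4, since question 3 has no 'No' or 'Nothing' option.
- Outside the main CC rule, a pattern with a positive experience answer and a positive tone answer goes to the CC conflict rule.

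Main CC: 1 × 1 × 3 × 4 × 3 × 4 = 144 (three non-'Awake' answers to question 3; questions 4 to 6 free). Main DC: 1 × 1 × 3 × 2 × 3 × 4 = 72 (question 4 limited to 'Not sure' or 'Nothing').

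| Rule | Patterns | Dream | Unconscious | Not sure | No dream answer |
|---|---|---|---|---|---|
| CC main | 144 | 48 | 48 | 48 | 96 |
| CC conflict | 912 | 336 | 288 | 288 | 576 |
| DC main | 72 | 24 | 24 | 24 | 48 |
| DC fallback | 96 | 36 | 30 | 30 | 60 |

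No rule requires a dream answer. The counts describe what the rules allow; they are not probabilities.

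**Step 4: does anything else establish dreaming?** Loss of responsiveness is three minutes without key presses, speech or spontaneous movement (section 2.2). Eye monitoring interrupts the scan if the eyes open, and 'Awake' reports are excluded (section 2.3). These bear on responsiveness and wakefulness. None shows that a dream was in progress.

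**The case against.** Several counter-arguments have force.

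- **The missing dream requirement is not peculiar to CC.** DC lacks it too, as the table shows. A reader might infer that DC sessions are guaranteed an inner experience while CC sessions are not. The rules do not support that: a non-tone external sensation, or 'Environment' at question 5, can satisfy DC. The asymmetry is only that tones can count as the experience in CC.
- **Tone perception may be legitimate CC.** The Introduction allows for stimuli perceived in a dream-like state as well as stimuli woven into a dream. Some tone-only reports may belong in CC. This stands, but the rule cannot tell which ones.
- **Participants are briefed on the questions in advance.** The briefing's content is not in the article, so it may affect how question 1 is understood. That tone-only listeners answer 'Yes' is the natural reading of the wording, not a documented fact.
- **Arousal is partly addressed.** It would go too far to say that near-wake listeners pass freely into CC, given the safeguards in step 4 and the model covariates. These safeguards still do not make the two groups alike in dream content.
- **Within-session contrasts offer protection.** Section 2.9 contrasts sound with silence and deviant with standard. A constant shift linked to dreaming would cancel there; only a change in the response to sound would bias those results. The protection is less clear for the spectral analysis, because section 2.9.6 compares peak-frequency series directly between CC and DC.

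**Conclusion.** The concern holds in this form: the written rules allow tone-only sessions without a dream answer to be called connected dreaming, DC needs experience beyond the tones, and neither group must report a dream. The Discussion's assurance of a shared dream-like state therefore claims more than the classification delivers, and the CC–DC contrast can mix sensory connection with the presence of other experience.

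The size is unknown. The documents give neither the share of tone-only CC sessions nor the effect of dream content on the BOLD measures. A reader might multiply an assumed share of 20% to 50% by an assumed shift of 0.5 SD to get 0.10 to 0.25 SD, and set that against the planned 0.85. The documents do not support this. Both inputs are invented, the 0.85 comes from event-related potentials in REM sleep (section 2.8), and a constant shift would cancel in the sound contrasts. The conclusion rests on the printed rules and on reading question 1 as including the tones.

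**What to change.** 1. Prespecify a CC–DC analysis restricted to question 3 = 'Dream' in both groups, and report it beside the main contrast.
2. Using questions 3, 5 and 6 as already collected, tabulate by group the question 3 answers and the number of tone-only CC sessions.
3. Do not class 'Unconscious' at question 3 as connected dreaming without treating it as a conflicting answer. State how that conflict is settled, because the present conflict rule would return the session to CC.
4. Make the conclusion about a shared dream-like state conditional on the restricted and main analyses agreeing. Otherwise, reword the Discussion to say that both groups were unresponsive and did not report being awake.
5. Leave question 1 as worded. Naming the tones there, before question 2, could cue the answer on connectedness.

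No new data are needed. The cost is fewer sessions from both groups, and so lower precision, in the restricted analysis. 'Dream' is also a self-label that some participants who were only thinking may not choose, which is why the restricted analysis should accompany the main contrast and not replace it.

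### The fallback rule for disconnected consciousness cannot be met as written, and once corrected it still lets one follow-up answer outweigh two denials of consciousness

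*Protocol article*

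**What the plan says.** All of this is in section 2.3 (Interviews following ROR) of the protocol article.

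- **Primary rules.** 'Yes' to questions 1 and 2 gives CC. The counterpart is "disconnected consciousness if participants replied “Yes” to question 1 and “No” to question 2".
- **Fallback CC rule for conflicting answers.** It needs a positive answer on experience (question 1, 5 or 6, or a dream at question 3) "in addition to a positive response to at least one question amongst numbers 2 and 4".
- **Fallback DC rule.** It opens: "If participants replied with “No/Nothing” to question number 2–4 and positively to at least one of the questions investigating their experience". The experience part is an answer given "positively to at least one of the questions investigating their experience (i.e., question number 1,3,5,6").
- **Options at question 3.** The list reads "having a dream or unconscious? Awake/Dream/Unconscious/Not" sure. It contains neither 'No' nor 'Nothing'.
- **No recall.** "State 1 will be discarded as it cannot be classified in either of the two categories of interest in this study".
- **Roles of the questions.** Questions 1 and 3 are to establish whether the participant was conscious, and question 2 whether connected. Questions 4 to 6 add detail and serve "to check the consistency of the reports".

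Section 2.7 names the resulting CC/DC condition as an independent variable of the study.

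**The concern.** The fallback DC rule conflicts with the answer list, because question 3 cannot be answered 'No' or 'Nothing'. It also conflicts with itself, because it puts question 3 in the block that must be negative and in the block that may be positive. An analyst has to guess what was meant, and the guess decides whether some sessions enter DC or drop out.

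Correcting the range leaves a second difficulty. One positive answer among questions 1, 3, 5 and 6 is enough, so a follow-up item can outvote both questions that are meant to establish consciousness. Such a session looks more like State 1, which is discarded, than like DC.

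The CC-versus-DC contrast underlies the study's hypotheses, and section 5 gives separating DC from unconsciousness as an aim. Unconscious sessions in the DC group would work against that aim and could weaken the contrast.

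**Working it through.** **Inputs.** The answer options and rules are from section 2.3. The effect size d = 0.85, allocation 1:1, two-sided alpha 0.05, power 0.95 and total of 74 sessions are from section 2.8 (the calculation based on REM sleep).

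**Number of patterns.** Questions 1 to 6 have 4, 3, 4, 4, 3 and 4 options: 4 × 3 × 4 × 4 × 3 × 4 = 2304. I excluded 'Awake' at question 3 first, then applied the CC rules, then the DC rules.

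**Step 1: the rule as written.** It needs question 2 'No', question 3 'No/Nothing' and question 4 'Nothing'. No option at question 3 fits, so 0 patterns qualify. DC then comes only from the primary rule. With question 1 'Yes', question 2 'No', question 3 not 'Awake' and no tone count at question 4, that gives 3 × 2 × 3 × 4 = 72 patterns. Another 456 patterns contain a positive experience answer but receive no class.

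**Step 2: reading '2 and 4'.** Fix question 2 'No' and question 4 'Nothing', with question 1 not 'Yes' (3 options), question 3 not 'Awake' (3), question 5 (3) and question 6 (4): 3 × 3 × 3 × 4 = 108. Remove those with no positive experience answer, 3 × 2 × 1 × 2 = 12. This leaves 96. DC rises to 72 + 96 = 168 patterns, and the unclassified fall to 456 − 96 = 360.

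**Step 3: the override under '2 and 4'.** Take question 1 'No' or 'Nothing' (2 options), question 3 'Unconscious' (1), question 5 (3) and question 6 (4): 2 × 1 × 3 × 4 = 24. Remove those with nothing positive at 5 or 6, 2 × 1 × 2 = 4. This leaves 20 DC patterns.

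- Decided by question 5 alone: 2 × 2 × 2 = 8.
- Decided by question 6 alone: 2 × 1 × 2 = 4.
- Both positive: 2 × 2 × 2 = 8.

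So 12 of the 20 rest on a single answer. Example: 1 No, 2 No, 3 Unconscious, 4 Nothing, 5 Myself, 6 Nothing gives DC.

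These are counts of possible patterns, not expected frequencies.

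**Step 4: possible effect on power.** The plan's own figure first: with 37 + 37 sessions the noncentrality is 0.85 × √(37 × 37 / 74) = 3.656 and the critical t on 72 df is 1.993, giving power 95%. This agrees with section 2.8.

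The documents give no rate of conflicting answers. Assume that a share m of DC sessions is mislabelled, that these sit at the CC mean, and that the standard deviation is unchanged. Then d becomes 0.85 × (1 − m):

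| m (assumed) | d | Noncentrality | Power |
|---|---|---|---|
| 0% | 0.850 | 3.656 | 95% |
| 5% | 0.8075 | 3.473 | 93% |
| 10% | 0.765 | 3.290 | 90% |
| 20% | 0.680 | 2.925 | 82% |

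**Step 5: price of removing such sessions instead.** Keep d = 0.85 and shrink only the DC group. At 10%, 37 − 4 = 33: noncentrality 0.85 × √(37 × 33 / 70) = 3.550, power 94%. At 20%, 37 − 7 = 30: 0.85 × √(37 × 30 / 67) = 3.460, power 93%.

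**The case against.** The strongest defence is that the intent is plain. The parallel CC rule names questions 2 and 4, and the DC sentence itself lists question 3 among the experience items. The primary rules do not depend on the faulty range. Letting later questions settle a conflict is deliberate, applies to CC as well as DC, and suits a setting where section 5 warns that amnesia may hide real experience. Participants learn the questions and options beforehand, and questions 5 and 6 both offer 'Nothing'.

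Most of this stands, and it rules out several stronger readings that a reader might infer:

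- *That the main variable is misassigned throughout.* Taken literally, the faulty rule leaves sessions unassigned. It does not label them wrongly.
- *That the faulty range itself puts self-declared unconscious participants into DC.* This requires taking 'Unconscious' as the negative answer to question 3, which would admit 30 patterns. No text says so, and listing question 3 among the possible positives points the other way.
- *That questions 5 and 6 force an answer.* Only the missing 'Not sure' at question 5 remains of this.
- *That a tone count at question 4 should not override 'No' at question 2.* Section 2.3 uses nearly this case as its example of what the later questions are for.
- *That 'Not sure' at question 2 with 'Nothing' at question 4 is a hole in the rules.* It falls out as unclassified, which is a reasonable result.
- *That power falls as under d × (1 − 2m), to 58% at m = 20%.* That formula describes equal swapping between CC and DC. The problem here adds sessions to DC only.

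The defence does not answer two points. An operative rule for an independent variable should not need to be inferred. And section 2.3 does not say why a denial at question 1 together with 'Unconscious' at question 3 should yield to one answer at question 5 or 6.

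**Conclusion.** The concern holds in two limited parts.

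First, the fallback DC rule is inoperable as written. The choice of reading moves 96 answer patterns between DC and no class. This follows from the text alone.

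Second, after the evident correction, 20 DC patterns combine a denial at question 1 with 'Unconscious' at question 3, and a single answer decides 12 of them. This conflicts with the roles given to questions 1 and 3 and with discarding awakenings without recall.

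The practical size is unknown. The power figures of 93%, 90% and 82% at 5%, 10% and 20% rest on an assumed share, on mislabelled sessions sitting at the CC mean, on sessions treated as independent in an equal split, and on d = 0.85 borrowed from an EEG sleep study. They illustrate a possible loss and do not predict one. The point merits correction before labels are applied, but it does not invalidate the classification.

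**What to change.** In section 2.3:

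1. In the fallback DC rule, change the range '2–4' to '2 and 4', matching the fallback CC rule.
2. For the main DC label, send sessions with 'No' or 'Nothing' at question 1 and 'Unconscious' at question 3 to State 1.
3. Keep the any-positive rule as a sensitivity analysis, and add a second one restricted to sessions with concordant answers. Making the concordant set the main analysis is a debatable trade-off and is not needed here.
4. Settle this before any session is labelled.

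The cost is a few lines of text and a few discordant sessions leaving DC. There is little slack: 80 planned sessions less 8% is 80 × 0.92 = 73.6 against 74 required, and State 1 and 'awake' sessions are discarded as well. Under the assumptions in the working, removing 10% of the DC group leaves power near 94%, against about 90% if those sessions stayed in and were mislabelled. If the removed sessions were in truth DC, the drop from 95% to 94% would be a pure loss, and the any-positive sensitivity analysis would help to show whether the conclusion depends on them.

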
### fMRI experimental design and auditory paradigm

2.4

We chose a mixed block/event-related design (Figure 3) in which trials of auditory stimuli are interspersed with blocks of silence of varying durations (15 blocks in total, each lasting 45 s and containing 30 trials on average). This design allows for the simultaneous modelling of the transient, trial-related activity, and the sustained, task-related BOLD activity. That is, by alternating silence blocks with task blocks (i.e., blocks with trials with auditory stimuli) we can optimize the sensitivity for discriminating events within trials and all events combined within a block. Blocks with only standard events will be alternated with blocks containing both standard and deviant events. Standard and deviant blocks will alternate in pseudorandomized order (ABBA…), in which no more than two identical types of blocks can follow one another. The length of the silence blocks will be randomized in 1-s steps in intervals of 7–10 s. Based on previous studies (Bekinschtein et al., 2009), each event (both standard and deviant sounds) will lasts 0.05 s; inter-stimulus interval (ISI) will be fixed at 0.1 s and inter-trial interval (ITI) will be jittered in 0.05-s steps between 0.7 to 1 s. We will use a variant of the “classic oddball” paradigm (Figure 3), in which trials will consist of a randomized number of repetitions (i.e., 3–5) of standard events plus one deviant event. Standard sounds will have a frequency of 100 Hz and deviants of 500 Hz. The total length of the auditory stimulation will be 15 min. Each task block will last 45 s (to have both a frequency still below the recommended 128 s high-pass filter, but also a reasonable number of trials). The parameters selected for the auditory stimulation are the result of the efficiency and collinearity analyses we performed to optimize the efficiency of our design. Sounds will be delivered via a Serene Sound Digital MRI-compatible system.

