### Preprocessing and statistical analysis

2.9

As we will use a mixed block/event-related design, all the following analyses (see Table 1 for a summary) will be conducted on the BOLD time-series at both the block and trial level: for the block-level analyses, we will contrast (1) task blocks (i.e., standard and deviant blocks combined) with silence blocks and (2) standard vs. deviant blocks. For the trial-level analysis, we will contrast (1) combined deviant and standard trials with BOLD extracted time-series of simulated time points during silence blocks and (2) deviant vs. standard trials. For the purpose of this project and the hypotheses presented, the analysis of RS data will not be discussed in this study.

**Table 1 tab1:** Hypotheses tested and corresponding analyses. This table provides a comprehensive overview of the analyses, brain areas, atlas employed, and statistical methods used for each hypothesis tested in this study.

Hypotheses tested	Analyses	Considered brain areas	Atlas	Statistical analysis
*Hypothesis 1*	Activation analysis (ROI-based)	All 7 sub-thalamic regions (L/R)	Oxford thalamic connectivity atlas	Small volume correction
*Hypothesis 2*	Activation analysis (ROI-based)	Primary auditory cortex (L/R): Heschl’s gyrus	Harvard-Oxford cortical and subcortical structural atlases	Small volume correction
*Hypothesis 3*	Activation analysis (ROI-based)	Secondary regions (L/R): superior temporal gyrus (both anterior and posterior division)	Harvard-Oxford cortical and subcortical structural atlases	Small volume correction
*Hypothesis 4*	ROI-to-ROI based connectivity	2 sub-thalamic (sensory and temporal) nuclei and Heschl’s gyrus	Oxford thalamic connectivity atlas/ Harvard-Oxford cortical and subcortical structural atlases	Subject-level: wGLM Group-level: LME
*Hypothesis 5*	ROI-to-ROI based connectivity	Heschl’s gyrus and superior temporal gyrus (both anterior and posterior division)	Harvard-Oxford cortical and subcortical structural atlases	Subject-level: wGLM Group-level: LME
*Hypothesis 6*	Voxel-to-voxel connectivity	Whole cortical and subcortical brain matters	No atlas	Subject-level: Intrinsic connective analysis Group-level: LME

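### At one trial about every 1.5 s, the design cannot in practice separate transient trial activity from sustained block activity for sounds versus silence, although section 2.4 says that it can

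*Protocol article*

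**What the plan says.** Section 2.4 of the protocol article justifies the mixed block/event-related design with this sentence: "This design allows for the simultaneous modelling of the transient, trial-related activity, and the sustained, task-related BOLD activity". The same section fixes the timing:

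- Blocks: "15 blocks in total, each lasting 45 s and containing 30 trials on average".
- Sounds: "each event (both standard and deviant sounds) will lasts 0.05 s".
- Gaps: "inter-stimulus interval (ISI) will be fixed at 0.1 s and inter-trial interval (ITI) will be jittered in 0.05-s steps between 0.7 to 1 s".
- Trial content: "trials will consist of a randomized number of repetitions (i.e., 3–5) of standard events plus one deviant event".
- Baseline: "The length of the silence blocks will be randomized in 1-s steps in intervals of 7–10 s".

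Section 2.9 states that the analyses "will be conducted on the BOLD time-series at both the block and trial level". At block level it contrasts all task blocks with silence, and standard with deviant blocks. At trial level it contrasts all trials with simulated time points in silence, and deviant with standard trials.

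Section 2.5 reports efficiency for the standard response, the deviant response and their difference, and collinearity between standard and deviant events. It reports no collinearity between trial and block regressors.

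**The concern.** Mixed designs separate transient from sustained activity only if events are spaced widely or irregularly enough within a block for the event regressor to depart from the block regressor. Here trials follow each other closely for the whole block, and the jitter spans only 0.3 s ("inter-trial interval (ITI) will be jittered in 0.05-s steps between 0.7 to 1 s"), which is small against a haemodynamic response lasting many seconds. Such a train convolves to something close to a boxcar.

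If so, the block-level and trial-level results for sound versus silence are nearly one test reported twice. Agreement between them could be read as confirmation, and a difference between connected and disconnected consciousness could be labelled transient or sustained without support. If both sets of regressors were entered together, as the word simultaneous invites, most of the precision would be lost.

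**Working it through.** **1. Timing (section 2.4).** A trial has 4 to 6 sounds, 5 on average.
- Mean trial length: 5 × 0.05 s + 4 × 0.1 s = 0.65 s.
- Mean inter-trial interval: (0.7 + 1)/2 = 0.85 s.
- Mean cycle: 0.65 + 0.85 = 1.5 s.
- Trials per block: 45/1.5 = 30, which reproduces the stated average.

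Reading the inter-stimulus interval as onset to onset would give 45/1.3 = 34.6, so it is the gap between sounds.

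**2. Simulation.** Forty sequences were built to the stated design: 15 blocks, 7–10 s silences, and pseudorandom order with at most two identical blocks in a row. Trial onsets, single sounds and block boxcars were convolved with a double-gamma canonical response (assumed), sampled at TR 0.842 s (section 2.5) and high-pass filtered at 128 s.

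Mean correlations, with every trial in a deviant block ending in a deviant:

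| Pair of regressors | r |
|---|---|
| All trials, all task blocks | 0.976 |
| All sounds, all task blocks | 0.985 |
| Deviant trials, deviant blocks | 0.989 |
| Deviant sounds, deviant blocks | 0.994 |

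**3. Joint model.** Variance inflation is 1/(1 − R²), and its square root multiplies the standard error.
- One trial and one block regressor: 1/(1 − 0.9763²) ≈ 21, so about 1/21 ≈ 5% of each regressor's variance is its own.
- Both sound types plus both block types: 29 (standard sounds), 89 (deviant sounds), 34 (standard blocks) and 115 (deviant blocks). Square roots: 5.4, 9.4, 5.8 and 10.7. Other rebuilds of the same design gave values within about 30 to 130.
- Contrasts in a trial-plus-block model, against either set alone (30 sequences): the standard error is multiplied by about 4.7 for the mean trial or mean block effect, and by about 8.4 for deviant minus standard.

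**4. Separate models.** Fitted alone, the event model is well conditioned. Standard and deviant sounds correlate at 0.31, so variance inflation is 1/(1 − 0.31²) ≈ 1.1.

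**5. Sensitivity to the layout of deviant blocks.** If half the trials in a deviant block carry a deviant (assumed), r between deviant sounds and deviant blocks is about 0.74 to 0.76 across rebuilds. Deviant-sound variance inflation is then about 3, and the standard error of deviant minus standard trials rises only 1.4-fold. The all-trials and all-sounds correlations do not change (0.976 and 0.985).

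**6. Other sensitivities, all trials against all task blocks.**
- No high-pass filter: r = 0.976.
- Inter-stimulus interval read as onset to onset: 0.983.
- 17 blocks instead of 15: 0.977.
- Silences of 15–20 s: 0.988.
- Inter-trial interval of 2–6 s, for illustration only: 0.71.

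Trial spacing is what drives the overlap.

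**The case against.** **The large inflation figures need a joint model that the analysis sections do not clearly specify.** This stands. Section 2.9 lists block-level and trial-level contrasts separately, section 2.9.2 speaks of block/trial levels, and section 2.9.5 has one stimulus/block-type factor. Only the wording in section 2.4 points to a joint fit. The inflation is therefore a reason not to fit that model, not a description of a planned one.

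**No hypothesis predicts a transient-versus-sustained difference, and nowhere is agreement between levels called confirmation.** True. It limits the harm to the stated property of the design and to how duplicated results will be read.

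**The deviant-specific figures depend on the block layout.** This also stands. The trial definition in section 2.4 favours a deviant in every trial of a deviant block, but other wording leaves room for a mixture and Figure 3 was not available to this review. The deviant part must be stated conditionally.

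Three stronger readings are tempting and unsupported:

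- A reader might argue that the trial rate (1/1.5 = 0.67 Hz) exceeds the sampling limit at this TR (1/(2 × 0.842) = 0.594 Hz). That is beside the point. Regressors are convolved before sampling, and a shorter TR would not remove the overlap.
- A reader might infer that the joint model cannot be fitted. It can, because the regressors are not identical. However, the small unshared part depends on the assumed response shape.
- A reader might want the block level to decide every hypothesis. Hypothesis 7 uses spectrograms without event or block regressors, and the connectivity analyses (Hypotheses 4 to 6) were not simulated.

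**Conclusion.** The point holds in limited form. For sounds versus silence, the trial and block regressors correlate at about 0.98 to 0.99, so the general transient and sustained effects are not separable in practice and the sentence in section 2.4 claims a property that the design lacks. This rests on the stated timing and an assumed canonical response. It does not depend on the filter, on how the inter-stimulus interval is read, on the number of blocks, or on how many trials in a deviant block carry a deviant.

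For deviant versus standard, the same is true (r about 0.99) only if every trial in a deviant block carries a deviant. With an assumed 50%, that effect is separable.

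A joint event-plus-block model under the first reading would make standard errors of individual regressors about 5 to 11 times larger. The check in section 2.5 does not answer this, since it compared only the two event types. The planned separate models remain valid, but they are not two independent pieces of evidence.

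**What to change.** - Replace the sentence in section 2.4 with a statement that the design does not separate transient from sustained activity for sounds versus silence.
- State that event and block regressors will not be entered in one first-level activation design matrix.
- For the activation analyses (Hypotheses 1 to 3), name one level in advance as deciding for sound versus silence. Report the other as a re-parametrisation of the same signal, not as independent confirmation.
- State whether every trial in a deviant block carries a deviant. If so, apply the same rule to deviant versus standard.

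The cost is the claim of separate transient and sustained effects, plus the choice of a deciding level before analysis. No change to the paradigm, the scanning or the sample is needed.
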